## Abstract

**Objective:**

This study aims to evaluate the implementation i.e., reach, adoption, fidelity, and maintenance; and effectiveness on blood pressure reduction of implementation strategies to enhance uptake of community-based hypertension control intervention in Nepal.

**Study design:**

A cluster randomized, hybrid type III effectiveness-implementation trial.

**Methods:**

The study focuses on Reach, Effectiveness, Adoption, Implementation, and Maintenance of the RE-AIM framework implementation outcomes. We will conduct a cluster randomized trial in Sindhupalchowk district, randomizing 102 health facilities in the district into the CHPC intervention (n = 51) and standard care control (n = 51) groups. The CHPC includes community-based BP monitoring, lifestyle counseling and medication adherence monitoring. The implementation strategies of CHPC intervention will include a) leadership support and ongoing program promotion, b) capacity building of healthcare workers and Female Community Health Volunteers (FCHVs) in hypertension management, c) FCHV group meetings and home visits, and d) creating social networks to promote shared learning. Participants (n = 3,572, 35 in each of the 102 clusters) aged ≥30 years with BP ≥ 140/90 mmHg and/or on medications will be recruited. Participants from intervention clusters will be assessed against those residing in the control communities. Implementation outcomes (reach, adoption, implementation and maintenance) will be assessed using data from the process evaluation in intervention health facilities. The evaluation will use a mixed-method approach. For effectiveness, the mean decrease in systolic BP in the intervention group compared to the control group will be assessed 12 months after the intervention begins. The cost-effectiveness of the intervention will also be assessed. We will conduct observations, periodic reflections, focused group discussions and key informant interviews to explore implementation outcomes. Qualitative methods will be informed by the Consolidated Framework for Implementation Research (CFIR) and analyzed using a rapid qualitative analytic approach and thematic analysis.

**Discussion:**

This study will provide evidence for tested approaches and mechanisms for utilizing and embedding community health volunteers in hypertension care to mitigate hypertension burden and improve quality of life.

**Protocol version:**

2; October 2024.

**Trial registration:**

ClinicalTrials.gov NCT06081010*. Registered 12 October 2023,*https://clinicaltrials.gov/study/NCT06081010.

## Introduction

1

Hypertension (HTN) is a significant global public health challenge, responsible for 13.5% of premature deaths, 54% of incident stroke, and 47% of Coronary Heart Disease (CHD) worldwide [1]. Of the estimated 1.2 billion adults with HTN globally, two-thirds live in low-and middle-income countries (LMICs) [2]. In Nepal, HTN affects 25% of adults [3], yet 44% remain unaware of their condition [4]. Among those diagnosed, only 33% receive treatment, and 12% achieve BP control [3,4].

Evidence-based interventions, such as weight loss [5], dietary modification [6], increased physical activity [7], lowered alcohol consumption [8] and consistent use of anti-HTN medications [9] remains the cornerstone of HTN prevention and control [10]. However, despite these interventions being proven effective, they have not yet been comprehensively translated into practice. Nepal adopted the Package of Essential Non-Communicable Diseases to strengthen HTN detection and management at primary healthcare facilities [11]. However, recent evaluations of PEN have identified multiple implementation barriers, including low perceived susceptibility, low health literacy, and misconceptions about HTN and its medications at individual level; peer pressure that supports physical inactivity and a high sodium diet at interpersonal level; norms supporting unhealthy eating and low medication adherence at community level; and unfilled human resource positions, overburdened healthcare staff, interrupted medical supplies and medicines, inefficient recording and reporting, and insufficient provider-patient interaction at health system level [[12], [13], [14], [15]].

To overcome these multi-level implementation barriers, we propose a community-based HTN management through FCHVs. FCHVs are trained community health volunteers [16], who have played critical roles improving maternal and child health in Nepal [17]. Emerging evidence suggests FCHV-led HTN control interventions can effectively improve hypertension outcomes, for example, a major trial in Nepal reported significant reductions in systolic and diastolic BP at one year among intervention participants as compared to controls (−4.90 mm Hg [−7.78, −2.00] and −2·63 mm Hg [−4·59 to −0·67], respectively) [18].

FCHVs led HTN managment is expected to address the implementation barriers in three ways. First, FCHVs will frequently engage with and educate patients with HTN, promoting their self-efficacy and empowering them to mitigate peer pressure and overcome negative cultural beliefs thus leading to a better quality of life. Second, FCHVs will improve health system efficiency by monitoring patient lifestyle behaviors, blood pressure, and medication adherence; and third, FCHVs will directly connect HTN patients with health care providers at health facilities through timely referrals.

### Objectives

1.1

This study aims to implement and evaluate Community-based HyPertension Contro (CHPC) through FCHV mobilization within the framework of existing government healthcare systems. Specifically, we will **(a)** assess implementation outcomes of the CHPC at provider and health system levels, **(b)** assess its effectiveness compared to facility-based PEN on systolic blood pressure, and, **(c)** assess economic sustainability.

## Methods

2

This protocol has been developed and reported following the Standard Protocol Items: Recommendations for Interventional Trials (SPIRIT) and Standards for Reporting Implementation Studies (StaRI) guidelines [19].

### Study design

2.1

We will evaluate primarily Reach, Effectiveness, Adoption, Implementation and Maintenance (RE-AIM) framework [20] implementation outcomes and secondarily assess effectiveness outcomes. Primary implementation outcomes wil be measured in the intervention group. We will conduct a non-blinded two-arm cluster-randomized trial to assess the effectiveness of the intervention on mean systolic BP compared to the control group at 12 months. The health facility will be randomly assigned to the intervention or control group. The intervention arm will receive the community health worker (CHW) intervention and strategies, while the control arm will receive the standard of care.

### Site

2.2

We will conduct the study in Sindhupalchowk district, one of the largest districts in Bagmati province, Nepal, consisting of nine rural and three urban municipalities (Fig. 2). The district spans hills to mountain region, where geography that facility-based healthcare delivery. This setting offer the opportunity to evaluate the intervention across diverse terrains and rural-urban contexts. The district lies within the catchment area of Dhulikhel Hospital-Kathmandu University School of Medical Sciences, which will directly support the program and facilitate participant referrals when needed.

### Randomization

2.3

A total of 102 health facilities will undergo randomization, stratified by municipality (Fig. 1). To ensure allocation concealment, the study not involved in recruitment will pre-generate 10 random allocation sequences for each of the 12 municipalities, using a computer-based random number generator. Each sequence will be placed inside an opaque, sequentially numbered, sealed envelope. During a public event, a neutral stakeholder, not affiliated with the research team, will select one sealed envelope, which will decide the final allocation. This process will prevent research team from predicting or influencing the assignment.

**Fig. 1 fig1:**
[figure not shown]
CHPC trial design.

**Fig. 2 fig2:**
[figure not shown]
Study area, Sindhupalchowk District.

### Study participants

2.4

#### Health facilities and FCHVs

2.4.1

We will contact the health facilities assigned to the intervention group and invite them to participate in the study. FCHVs reporting to and providing services through these health facilities will be recruited with the support of the health facility in-charge.

#### Participants with HTN

2.4.2

Individuals aged 30 years and older (based on Nepal's PEN protocol) [21] with high BP (≥140/90 mmHg) [22] residing in Sindhupalchowk will be eligible for inclusion. Individuals with severe illness requiring bed rest and pregnant women will be excluded. Community screenings will be conducted to identify the individuals eligible to participate. Trained research assistants (RAs) will explain the study objectives, procedures, voluntary participation, and the right to withdraw at any time to eligible participants. Written informed consent will be obtained before participation. For illiterate participants, verbal consent will be obtained, and a caregiver or witness will sign the consent form.

### Intervention

2.5

The intervention involves task-shifting of HTN management roles to FCHVs, integrating the five components of the evidence-based interventions outlined in the PEN protocol-1 and 2 [21,23]:(a)BP measurement and monitoring;(b)Identify individuals with high BP and report to the health facility;(c)Provide one-on-one counseling and lifestyle modification goal setting, including sodium reduction, healthy diet, alcohol and smoking abstinence, physical activity, and medication;(d)Support medication adherence of HTN patients, delivered by the FCHVs trained for the intervention. The intervention will be conducted over a year and repeated during maintenance. The study is in the fourth quarter of the first year.

### Implementation strategies

2.6

Implementation of the PEN interventions faces multilevel barrires: low literacy and HTN misconceptions amongst individuals, communitynorms promoting unhealthy lifestyles and improper medicine use, and health systems constrains such as limited and overburdened staff and supply interruptions, limited provider-patient interaction time and weak recording and reporting system [[12], [13], [14], [15]].To address these barriers, we have designed the following coordinated implementation strategies (Table 1):a.**Leadership support, community engagement, and ongoing program promotion**: Ongoing support government leadership is critical to the successful implementation and sustainability of the CHPC. We wil form a steering committee consisting of representatives from central and provincial Ministries of Health (MoH), NCD experts, and health system experts. The committee will provide strategic guidance, oversee implementation, assess risks, and support sustainability planning. A Community Advisory Board, including people with HTN, community leaders, health staff, and political stakeholders will meet bi-to tri-annual basis. We will conduct project orientation at the province/district and municipal level, and health facility level. We will share the study progress in quarterly health system review meetings.b.**Capacity building:** There is a growing recognition that capacity building can be enhanced by supporting training with ongoing coaching and technical assistance [[24], [25], [26]]. We will first conduct the training of the trainers (ToT), where at least one healthcare worker from each facility along with municipal health coordinators, will be trained as a trainer. The trained healthcare workers will then train FCHVs to implement the intervention. FCHV training will occur at the start and midpoint of implementation year. For both healthcare providers and FCHVs, the 3 day training will focus on three objectives: 1) knowledge of the PEN protocols 1 and 2, 2) skills to implement the intervention including communications, patient engagement, and monitoring progress [27], and 3) skills for barriers management [28]. Training for health care workers will also include skills development to train FCHV and provide ongoing coaching and technical assistance. All training will follow participatory adult learning principles [27,28]. Furthermore, FCHVs will receive flipchart, BP instruments, and recording forms, and reporting sheets.

**Table 1 tbl1:** Implementation strategies’ core and adaptive components.

	Core components	Adaptive components
**Leadership support and ongoing program promotion**	Health Coordinators from the Provincial MoH will participate in the planning, execution and monitoring of the study. In provincial MoH health review meetings, hypertension-related indicators (proportion of population screened, HTN detected, HTN under medication, HTN control) will be discussed using the government's health management information system data.	Health coordinators will be encouraged to discuss how to engage patients and health workers in planning and monitoring CHPC. In review meetings, tip sheets will be provided listing the contextual challenges and possible solutions in achieving HTN screening, detection, medication, and control.
**Capacity building**	Healthcare workers training; FCHV training; Coaching and technical support from healthcare workers to FCHV in a monthly meeting	Health care workers can connect with the research staff on the telephone when needed; FCHVs can connect with healthcare workers on the phone when needed; FCHVs may be provided with the list and contact details of referral centers and related physicians to smoothen referral of patients with high BP
**FCHV Home visit and group meeting**	1st visit: introduction, rapport building, goal setting, BP monitoring; 2nd- 4th visit: BP monitoring, action and reflection, discussing problems faced in achieving their goals and implementing their action plans	Additional visits/meetings can be scheduled depending on patients' needs and FCHV's availability. May include family members who are decision makers during home visit session; May conduct the home visit session in groups living in the same household
**Social network**	Monthly meetings of health care workers in the municipality are held. Monthly meeting of FCHVs in the health facility.	May conduct experience sharing regarding the CHPC in meetings conducted for other purposes; May invite community leaders or patient representatives to the meetings

**Coaching and technical assistance**: We will provide ongoing support for FCHVs by training the healthcare workers to coach and supervise them. Research team members will attend the monthly meeting, offer phone support, and provide technical assistance. Healthcare workers will use monthly meetings and phone communication to support FCHVs. Furthermore, we will also connect intervention health facilities to the telemonitoring services of Dhulikhel hospital to support HTN case management and referrals, when needed.c.**FCHV group meetings and home visits:** After completing training and competency assessment, FCHVs will conduct group meetings and home visits. From the list of patients with HTN enrolled at screening, FCHVs will form HTN patient group and organize four sessions in a year. They will first invite HTN patients to attend group meetings, those with uncontrolled HTN, adherence challenges, or inability to attend will receive home visits. In the first visit (∼ 90 min), FCHVs will explain the purpose, monitor blood pressure, discuss HTN and its consequences, and provide education using flip chart. Participants will choose lifestyle goals including physical activity, healthy diet, tobacco and harmful use of alcohol, attending medical follow-up, BP monitoring, and antihypertensive medication use. In subsequent sessions (∼ 60 min), the FCHVs will measure BP, review progress, address challenges, and update action plans with participants and their family members.d.**Social network:** Using learning networks concept [29], we will facilitate information exchanges among healthcare workers and FCHVs to support shared problem-solving, learning and program implementation [30,31]. These exchanges will occur during regular municipal and health facility meetings. We will provide discussion questions, with healthworkers facilitating discussions.

### Outcomes

2.7

Following the Hybrid Type III effectiveness-implementation appraoch, this study assesses both implementation and clinical outcomes (Table 2). The primary implementation: Reach, Adoption, Implementation, and Maintenance [20] in intervention arm, measured at health facility level. The clinical outcome is the mean change in systolic blood pressure (SBP) between intervention and control arms from baseline to 12 months, measured at the participant level. Secondary clinical outcomes diastolic BP, control, awareness of HTN diagnosis, lifestyle practices, medication adherence, quality of life, and economic costs compared between intervention and control groups.

**Table 2 tbl2:** Study outcomes.

Implementation Outcomes			
		**Measures**	**Data Sources**
Reach	Percentage of FCHVs implementing the program participating in at least 8 of the 12 monthly meetings	At least 80% of the trained FCHVs will participate in at least 8 of the 12 monthly meetings;	Process tracking data, including the number of FCHVs participating in each group session meeting and themes discussed, as reported by the health facility in charge. Attendance records will be collected by study staff during monthly process tracking calls with the health facility in charge.
	Percentage of patients with hypertension in the community aware of their high BP status	At least 80% of the patients with hypertension in the community are aware of their diagnosis.	Participant survey
Effectiveness	Systolic BP (mmHg)	The net difference in mean systolic BP (mmHg) will be measured after 12 months between the intervention and control groups.	Baseline and end-line surveys
Adoption	Percentage of the health facilities intending to adopt the program.	Adoption will be a dichotomous measure (adopted vs not adopted). Adoption is defined as health facilities where FCHVs complete the initial FCHV training sessions	Process tracking data, FCHVs attending the training, based on attendance logs
Implementation	Percentage of the health facilities implementing the minimum standard of program implementation.	At least 80% of the health facilities will implement a minimum standard for program implementation. Implementation will be a dichotomous measure (successful vs inadequate). A health facility will be defined as having successfully implemented the program if: (1) health facility in charge conducts monthly coaching and technical support at least 8 out of 12 months in a year; (2) 80% of FCHVs conduct first home visits to at least the 80% of the target clients; (3) 80% of FCHVs conduct at least one group meeting with at least 80% of the target clients; and, (4) 80% of FCHVs submit monthly reports at least 8 out of 12 months in an implementation year. As secondary outcomes, we will also: ● assess the extent to which each core component was implemented and ● report the percentage of health facilities implementing all core components. ● explore facilitators and barriers to implementation.	Healthcare worker survey, Process tracking data: including a monthly checklist documenting intervention component completed, and HTN patients' participation in them, to be collected by the health facility in charge during standing monthly meetings with FCHVs. Meeting observations and periodic reflection interviews will be used to explore fidelity and the facilitators and barriers.
Maintenance	Percentage of the health facility implementing a minimum standard to program implementation during the maintenance period	At least 80% of the health facilities will implement a minimum standard for program implementation during the maintenance period. Implementation will be a dichotomous measure (successful vs inadequate). A health facility will be coded as having successfully implemented the program if: [1] The health facility in charge conducts monthly coaching and technical support at least 8 out of 12 months in a year; (2) 80% of FCHVs conduct first home visits of at least 80% of the target clients in the maintenance year; (3) 80% of FCHVs conduct at least one group meeting with at least 80% of the target clients in the maintenance year, and (4) 80% of FCHV submit monthly reports at least 8 out of 12 months in an implementation year. As secondary outcomes, we will also: ● assess the extent to which each of the individual core components were being implemented during the implementation phase, and ● Examine the percentage of health facilities that implement all core components.	Healthcare worker survey and process tracking data, including a monthly checklist documenting intervention component completed and HTN patients' participation in them, will be collected by the health facility in charge during standing monthly meetings with FCHVs. FGDs and KIIs will be used to explore the maintenance facilitators and barriers, as well as sustainability.
Effectiveness outcomes			
(A) difference between the intervention and control group at 12 months in		(1) mean systolic and diastolic BP (mmHg); (2) proportion of patients aware of their HTN diagnosis; (3) proportion of patients with controlled BP (i.e., less than 140/90 mmHg; (4) low physical activity i.e., less than 600 MET- minute; (5) intake of five or more servings of fruits and vegetables per day; (6) adherent to hypertension medication; (7) quality of life scores	The interviewer administered quantitative baseline and endline survey
(B) multiple economic and financial outcomes:	(i) affordability (cost), (ii) cost-effectiveness (iii) equity, and (iv) scalability (measured by the difference in cost per patient of CHPC compared to standard of care).	Affordability: measured by total incremental costs of care in the study arms; Cost-effectiveness: measured by calculation of incremental cost-effectiveness ratios (ICERs) per person for per BP control and per QALY gained; Equity (from patient-perspective): Household economic impacts in the study are measured by financial and economic costs. Disaggregated analysis, based on gender, ethnicity, and socio-economic status, will be conducted to assess disparities among the study groups. Scalability: Scenario-based and sensitivity analysis for scaling up this intervention at local, provincial and national levels.	The interviewer administered quantitative survey, including: ● Baseline and endline patient surveys; ● Facility based survey; ● Costing instrument to calculate total and component costs; ● Process tracking system; ● Weekly time logs.

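### The community awareness target under Reach is measured only in screened, enrolled participants, so meeting 80% cannot be credited to the programme's reach

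*Protocol article*

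**What the plan says.** Section 2.7 and Table 2 use awareness of hypertension twice.

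- **Reach (primary implementation outcome).** The target is "At least 80% of the patients with hypertension in the community are aware of their diagnosis", with "Participant survey" as the data source. Section 2.1 limits where it is judged: "Primary implementation outcomes wil be measured in the intervention group".
- **Effectiveness (secondary clinical outcome).** The "proportion of patients aware of their HTN diagnosis" is compared between intervention and control at 12 months, from the baseline and endline surveys. No 80% threshold is attached to this comparison.

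The people surveyed are described in three places.

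- Section 2.4.2: "Community screenings will be conducted to identify the individuals eligible to participate". Then "Trained research assistants (RAs) will explain the study objectives, procedures, voluntary participation, and the right to withdraw at any time to eligible participants", and consent follows. No difference between arms is stated.
- The Methods paragraph of the abstract widens entry beyond raised blood pressure: people with high readings "and/or on medications will be recruited".
- Section 2.6, item c, on how the intervention starts: "From the list of patients with HTN enrolled at screening, FCHVs will form HTN patient group".

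The article describes no separate sample of the community at endline.

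**The concern.** The target names one population and the data source reaches another. The target concerns all patients with hypertension in the community. The survey covers those who were found by the research team or were already treated, and who then agreed to join a hypertension study. People whom FCHVs identify outside that cohort, which is part of the intervention under section 2.5, do not enter the figure.

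The measurement process can also move the outcome. Someone who is screened, found eligible and has the aims of a hypertension study explained may learn of the condition that way. Someone already on medication presumably knew beforehand. Neither is the work of the programme.

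Two conclusions are at stake. A primary Reach benchmark could be declared met because of research screening and earlier care. And because controls go through the same screening, the awareness difference at 12 months may be smaller than the programme's effect would be in an unscreened population.

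**Working it through.** **Inputs.** Awareness target 80% (Table 2). Unaware share in Nepal 44% (Introduction), so 56% aware. 51 intervention facilities, 9 community health workers per facility, ICC 0.04, stated precision 4.2% (section 2.8.1). 35 patients per cluster and ICC 0.015 for the clinical outcome (section 2.8.1). About 60% of participants uncontrolled (section 2.8.1).

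**Step 1: the plan's own precision.** n = 51 × 9 = 459; design effect = 1 + (9 − 1) × 0.04 = 1.32.

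Half-width = 1.96 × √(0.80 × 0.20 × 1.32 / 459) = 0.042, which agrees with the stated 4.2%. This counts health workers, so it applies to the FCHV-meeting Reach item and not to patient awareness. For 51 clusters of 35 patients (n = 1,785) at 80%, the half-width would be about 2.3% with ICC 0.015 (design effect 1.51) and about 2.9% with ICC 0.04 (design effect 2.36). Precision is not the difficulty.

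**Step 2: how much screening-induced awareness meets the target.** Let a₀ be awareness before screening, and t the share of previously unaware participants who become, and stay, aware through screening and enrolment. With no programme effect:

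- endline awareness = a₀ + (1 − a₀) × t
- t needed for 80% = (0.80 − a₀) / (1 − a₀)

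| a₀ | t needed for 80% |
|---|---|
| 40% (assumed) | 0.40 / 0.60 = 66.7% |
| 56% (Introduction) | 0.24 / 0.44 = 54.5% |
| 70% (assumed) | 0.10 / 0.30 = 33.3% |

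The awareness of the enrolled mix is not given, so 40% to 70% is an assumption around 56%. The plan's 60% uncontrolled share gives it some footing. If the remaining 40% qualify through medication and all know their diagnosis, and a share u of the uncontrolled know theirs, then a₀ = 0.40 + 0.60u. That is 40% at u = 0 and 70% at u = 50%.

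**Step 3: room left for a difference between arms.** With a₀ = 56% and the same t in both arms, the share still unaware, which is all the programme can act on, is 0.44 × (1 − t).

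| t | Awareness without programme effect | Still unaware |
|---|---|---|
| 0% | 56% | 44% |
| 25% | 67% | 33% |
| 50% | 78% | 22% |
| 75% | 89% | 11% |
| 90% | 95.6% | 4.4% |

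If the programme informs a fixed fraction of those still unaware, the between-arm difference shrinks in proportion to the last column. At t = 50% it is half of what it would be without screening (22 / 44).

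**The case against.** A reader might infer that 80% is reached in both arms by design, whatever the programme does, and that at most 10 points are left for a difference between arms. The documents do not support this.

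- The 80% target applies to the intervention arm only. Controls enter through the 12-month comparison, which has no threshold.
- Section 2.4.2 does not say that participants are told a reading or a diagnosis. Disclosure is plausible but assumed. At t = 25% or 50%, awareness from a 56% start is 67% or 78%, both short of the target.
- A 10-point limit follows only if control awareness is assumed to be at least 90%, a figure with no source in the article.
- The article does not show how awareness is asked, and the questionnaire may settle that. If it means a diagnosis by a health worker, a research reading alone might not count. Reporting to facilities and referral by FCHVs could then produce a real difference.

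The weight is also limited. Awareness is one of two Reach items and one of several secondary effectiveness outcomes. Systolic blood pressure, its power, and the Adoption, Implementation and Maintenance targets are untouched.

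All of this stands. It does not repair the mismatch between a community target and a survey of enrolled participants. Nor does it separate programme reach from screening and earlier treatment. Treated patients make the target easier to meet, again without FCHV activity.

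**Conclusion.** The point holds as a mismatch between target and measurement. As described, the Reach awareness item cannot support a statement about the community, and a value of 80% or more in the intervention arm cannot be credited to the programme alone. From the document's 56%, it takes about 55% of previously unaware participants becoming aware through screening and enrolment to reach the target with no programme effect, or about 33% to 67% over the assumed starting range. The between-arm difference may be attenuated. By how much depends on t, which the article does not allow one to estimate.

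This rests on three assumptions: the participant survey is the survey of the enrolled cohort, with no community sample described elsewhere; screening and consent work alike in both arms; and the national 56%, or the range around it, is a fair starting point for this cohort.

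**What to change.** 1. Restate the Reach item and the effectiveness outcome as awareness among screened, enrolled participants.
2. Report endline awareness beside baseline awareness and the control-arm value. State whether the baseline question was asked before or after the screening reading, since a baseline taken afterwards may already include the effect of screening.
3. State that 80% will not be read as community reach, or as programme reach alone.
4. Add a patient-level Reach measure: the percentage of enrolled intervention participants with at least one FCHV group or home session. FCHVs already record these sessions (section 2.8, process tracking), and the monthly checklist in Table 2 covers patient participation.

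**Cost.** Outcome wording, and one summary from data already collected. The Reach claim becomes narrower, and the added measure partly overlaps Implementation criteria 2 and 3, which concern home visits and group meetings reaching target clients. Keeping the community claim would instead need an independent endline community sample, which is new fieldwork.

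Dropping the outcome or reordering the screening questions is not a clean remedy. Recruitment began in December 2024, so a new question order cannot help people already enrolled. The trial status section says that no outcome data have been accessed, so the relabelling can still be documented ahead of any analysis.

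### The Maintenance row of Table 2 contradicts itself on the time window: criterion (4) and the first secondary measure name the implementation period, not the maintenance period

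*Protocol article*

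**What the plan says.** Section 2.7 lists Maintenance among the primary implementation outcomes, and Section 2.8.1 makes an 80% rate the standard of acceptability. The Maintenance row of Table 2 sets its period twice before it lists any criteria. The outcome is "Percentage of the health facility implementing a minimum standard to program implementation during the maintenance period" and the target is "At least 80% of the health facilities will implement a minimum standard for program implementation during the maintenance period".

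A facility is then coded as successful or inadequate on four criteria joined by and:

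- Criterion (1): "The health facility in charge conducts monthly coaching and technical support at least 8 out of 12 months in a year".
- Criterion (2): "2) 80% of FCHVs conduct first home visits of at least 80% of the target clients in the maintenance year".
- Criterion (3): "3) 80% of FCHVs conduct at least one group meeting with at least 80% of the target clients in the maintenance year".
- Criterion (4): "4) 80% of FCHV submit monthly reports at least 8 out of 12 months in an implementation year".

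Two secondary measures follow. The first is to "assess the extent to which each of the individual core components were being implemented during the implementation phase". The second is to "Examine the percentage of health facilities that implement all core components", with no period attached.

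**The concern.** Within one row, the outcome, the target and criteria (2) and (3) point to the maintenance period, while criterion (4) and the first secondary measure point to the period before it. Criterion (1) points to neither.

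This matters because the row is the operational coding rule for a primary outcome, and all four criteria must hold. One criterion read from the wrong year can therefore change a facility's code. Two analysts, one applying criterion (4) as worded and the other applying the outcome definition, could classify the same facility differently from the same process-tracking data. Under the literal reading, part of an outcome meant to show sustained delivery would repeat a result already counted under Implementation.

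**Working it through.** **1. Are the two periods distinct?** Yes. Section 2.5 says that the intervention runs for a year and is repeated during maintenance. Section 2.8 (process tracking) names implementation and maintenance separately.

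**2. Periods named in the two rows of Table 2**

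| Item | Implementation row | Maintenance row |
|---|---|---|
| Outcome and target | none named | maintenance period |
| (1) monthly coaching | a year | a year |
| (2) first home visits | none named | maintenance year |
| (3) group meeting | none named | maintenance year |
| (4) monthly reports | implementation year | implementation year |
| First secondary measure | none named | implementation phase |
| Second secondary measure | none named | none named |

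The maintenance year was added to (2) and (3), while the periods in (1) and (4) match the Implementation row. For criterion (4) this looks like carried-over wording. The first secondary measure names a phase that its counterpart in the Implementation row does not name, so it is not a verbatim carry-over, but it still conflicts with its own row.

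**3. Does anything elsewhere repair it?** No. Section 2.9 refers back to Table 2 for these outcomes, and no other section moves criterion (4) or the first secondary measure to the maintenance year.

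**4. Literal coding against maintenance-year coding**, for a facility that meets (1) to (3):

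| Reporting in implementation year | Reporting in maintenance year | Literal code | Maintenance-year code |
|---|---|---|---|
| met | met | successful | successful |
| met | not met (even 0 of 12 months) | successful | inadequate |
| not met | met | inadequate | successful |
| not met | not met | inadequate | inadequate |

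Let a be the number of facilities in the second line and b the number in the third. With all 51 intervention facilities in the denominator, the literal percentage minus the maintenance-year percentage is (a − b)/51. One facility is worth 1/51 = 1.96 percentage points. The 80% target needs 41 facilities (0.80 × 51 = 40.8; 41/51 = 80.4%, 40/51 = 78.4%). The article gives no reporting rates, so neither a nor b is known, and neither the size nor the sign of the difference can be derived.

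**5. The plan's own figure.** Section 2.8.1 states 4.2% precision for 51 facilities, 9 community health workers each and an intraclass correlation of 0.04. Design effect = 1 + (9 − 1) × 0.04 = 1.32. Half-width at 80% = 1.96 × √(0.8 × 0.2 × 1.32 / 459) = 0.042, with 459 = 51 × 9. The figure reproduces and does not depend on this point.

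**The case against.** The best defence is that the row's own definition governs. The outcome and the target both name the maintenance period, and the row uses the word implementation generically, for delivery of the programme during maintenance. Criterion (4) also has an indefinite article, which fits loose wording better than a pointer to year 1. Much of this stands: the maintenance year is very probably what the authors mean. It does not remove the problem, because coding is done criterion by criterion and the text of criterion (4) names the other period.

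A reader might go further and infer that the trial has chosen to score maintenance on first-year reports. The documents do not support that. No section says that first-year reports will be carried forward, and the stated data source for Maintenance is a monthly checklist collected at standing meetings.

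A reader might also expect an inflated Maintenance percentage because reporting lapses once the implementation year ends. The article says nothing about lapsing, and the literal rule can err in either direction. Criteria (2) and (3) already require maintenance-year activity, so a facility that stops visits or group meetings fails whatever happens on criterion (4).

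The scope is limited too. Only the first of the two secondary measures names the wrong period, and it does not enter the coding. Criterion (1) is unanchored, not wrong.

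**Conclusion.** The point holds as an internal contradiction in the coding rule of a primary implementation outcome. Confidence is high that the wording conflicts. What would follow in practice depends on whether the rule is applied literally, which the documents do not settle.

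Under the literal reading, criterion (4) of Maintenance duplicates criterion (4) of Implementation: it credits past reporting to facilities that no longer report, and it permanently excludes facilities that reported poorly at first and later improved. No number can be put on the effect. Sample size, the stated precision and the blood pressure analysis are untouched. This is an error in stated text and not a detail left to an analysis plan, since the article gives the rule in full. It should be corrected before Maintenance is coded.

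**What to change.** In the Maintenance row of Table 2:

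- End criterion (4) with the maintenance year in place of the implementation year.
- Set the first secondary measure in the maintenance period in place of the implementation phase.
- For consistency, tie criterion (1) to the maintenance year.

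All four criteria and the first secondary measure then rest on maintenance-year process data only. The cost is a few words. No new data are needed, because process tracking already covers both periods (Section 2.8). The Trial status section states that no outcome data have been accessed, so the change can be made and recorded without knowledge of results.
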